**Figure 1 F1:**
[figure not shown]
**Flow chart**. LBP: low back pain; RMDQ: Roland-Morris Disability Questionnaire; MD: movement control dysfunction; TSK: Tampa Scale for Kinesiophobia; DEPS: a depression questionnaire; MCAQ: Motor Control AbilitiesQuestionnaire; SMQE: specific movement control exercise; MC: movement control: ManTher: manual therapy.

### Outcome measures

Baseline measures are taken of the one primary outcome (RMDQ), and four secondary outcomes (PSFS and Oswestry Disability Index, Movement control tests by Luomajoki, general health questions) prior to randomization.

Main outcome measure:

Roland-Morris Disability Questionnaire (RMDQ)

Secondary outcome measures:

Patient-Specific Functional Scale (PSFS) [61]

Oswestry Disability Index [62]

Movement control tests described by Luomajoki et al. [47]

The amount of absence from work with a questionnaire#

The need for other treatment modalities with a questionnaire#

The need for pain medication with a questionnaire#

Patient satisfactory with global assessment with a questionnaire#

# A questionnaire with three claims (less than usual, equal, more than usual)

### Statistical analysis

A sample size of 70 participants, determined a priori, provides 80% power by α 0.05 to detect an effect of change in disability based on three point difference with RMDQ, which we regard as minimal important difference for this outcome [63].

The comparability of the groups on prognostic and outcome variables at baseline will be analyzed using the two-sample t-tests for parametric and Wilcoxon test for non-parametric distribution as well as Chi-Square test for nominal data. Differences between the groups over time are measured with Mann Whitney *U *test. A regression analysis for predictive factors will be conducted on covariates at baseline. Statistical significance is set on α < 0.05. Statistical analyses will be done with SPSS for Windows release 17.0.

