### Interventions

Participants attend for up to five treatment sessions over an eight week period. The treatment is carried out by two different physiotherapists. The treatments are implemented as follows.

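### The article fixes neither the time point nor the score form of the primary RMDQ comparison that carries the 80% power and the 0.05 level, and the stated test does not adjust for baseline RMDQ

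*Protocol article*

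**What the plan says.** All references are to the protocol article.

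- **Outcome measures** fixes the variable: "Baseline measures are taken of the one primary outcome (RMDQ), and four secondary outcomes". It attaches no post-baseline time to the RMDQ.
- **Statistical analysis**, sample size: the planned total is 70, and the article says that this number "provides 80% power by α 0.05 to detect an effect of change in disability". The target is a difference of three RMDQ points, taken as the smallest that matters. No visit is attached to this change, and no standard deviation is given.
- **Statistical analysis**, between-group test: "Differences between the groups over time are measured with" the Mann-Whitney U test. This sentence covers the outcomes in general and does not name the RMDQ, but it is the only between-group outcome test in the article. A separate regression is planned for predictive factors at baseline.
- **Statistical analysis**, level: "Statistical significance is set on α < 0.05". No ordering or splitting of this level is given.
- **Interventions** gives the only time frame for the trial in the text: "Participants attend for up to five treatment sessions over an eight week period". It is described as a treatment period, not as an assessment.

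**The concern.** The outcome, the power statement and the test should all point to the same comparison. Here each leaves the time open. The phrase in the analysis sentence can mean the score at one follow-up, the change from baseline to one follow-up, or a test at every follow-up in turn. These are different analyses with different variances, and in the last case a different error rate.

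Two things are at stake. First, if there are several follow-ups, nothing in the text says which result answers the trial's question, so the choice could be made after the results are seen. The Background gives some reason to think that timing could matter. It describes specific and general exercise as comparable particularly in the longer term, with a possible short-term advantage for specific training. It also cites effect sizes from 0.43 (short term) to 0.14 (long term) for classification-matched treatment. Those last figures come from chronic low back pain and are the ends of a range, so they do not forecast this trial.

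Second, the baseline RMDQ is measured before randomization, but the stated test makes no adjustment for it. A rank test also does not in itself estimate the difference in RMDQ points, which is the scale on which the three-point target is set.

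**Working it through.** **Inputs from the Statistical analysis section:** N = 70, power 80%, α = 0.05, difference 3 RMDQ points, Mann-Whitney U test.

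**Assumptions (not in the article):** 35 per arm, two-sided tests, k follow-ups each tested at 0.05, and equal correlation ρ between visits.

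**1. The plan's own figure.** N = 70 cannot be reproduced without a standard deviation (SD), but the SD it implies can be found. With n = 35 per arm,

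SD = δ / [(z₀.₉₇₅ + z₀.₈₀) × √(2/n)] = 3 / [(1.960 + 0.842) × √(2/35)] = 3 / (2.802 × 0.239) ≈ 4.48.

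A one-sided test would imply 5.05. Two-sided with 10-20% dropout would imply 4.25 to 4.01. The figure is plausible, but the text does not say whether this SD belongs to a follow-up score or to a change score, or at which visit.

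**2. Why the form matters.** Let the SD σ be equal at baseline and follow-up, and let r be the baseline-to-follow-up correlation (assumed). The variances per person are σ² for the follow-up score, 2(1 − r)σ² for the change, and (1 − r²)σ² for the baseline-adjusted comparison (ANCOVA).

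| r | Change / follow-up score | ANCOVA / follow-up score | ANCOVA / change = (1 + r)/2 |
|---|---|---|---|
| 0.3 | 1.40 | 0.91 | 0.65 |
| 0.5 | 1.00 | 0.75 | 0.75 |
| 0.7 | 0.60 | 0.51 | 0.85 |

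The same 70 participants therefore give different power depending on the form chosen. The adjusted comparison has the smallest variance in every row.

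**3. One follow-up, one change score.** A simulation of 20,000 null trials with 35 per arm and a two-sided Mann-Whitney test gave a false-positive rate of 4.8%, in line with the nominal 5%. With SD 4.48 and a true difference of 3, its power was about 77%, against 80% for a comparison of means.

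**4. Several follow-ups, each at 0.05.** If the visits were independent, the chance of at least one false positive is 1 − 0.95^k, which is 9.75% for k = 2 and 14.3% for k = 3. Repeated measures are correlated, so the rate was simulated in two ways: Mann-Whitney tests in 20,000 null trials, and correlated normal test statistics with 500,000 draws.

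| k | ρ | Mann-Whitney | Normal statistics |
|---|---|---|---|
| 2 | 0.5 | 8.8% | 9.0% |
| 2 | 0.7 | 8.4% | 8.4% |
| 2 | 0.9 | 6.8% | not run |
| 3 | 0.5 | 12.3% | 12.5% |
| 3 | 0.7 | 11.2% | 11.0% |
| 3 | 0.9 | 8.1% | not run |

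**5. Price of the alternative.** If all visits were kept as co-equal with a Bonferroni split, at SD 4.48 the N for 80% power would be 86 (k = 2) or 94 (k = 3). Power at N = 70 would fall to 71% or 66%. Naming one visit avoids this cost.

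**The case against.** A reader might infer that a two-sample rank test cannot compare groups over time, and that the plan as written exceeds 5% error. The documents support neither.

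- Mann-Whitney on the change from baseline to one visit is a valid comparison over time. The sample-size sentence speaks of change in disability, which favours that reading, and the baseline RMDQ it needs is collected. The limit of the test is narrower: it cannot model several visits jointly or test a group-by-time interaction.
- The error inflation needs at least two post-baseline RMDQ tests. The text states no number of follow-ups, and with one follow-up the rate is 5%.
- Figure 1, the flow chart, was not available for this check and may hold the assessment schedule. If it shows a single follow-up, that visit is primary by default. Its absence here is no fault of the plan.
- An article condenses the full protocol, and multiplicity rules and model details commonly sit in the analysis plan.

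All four points stand, and they make the error figures conditional. They do not remove the defect. The sentence that names the test is written down, and it does not identify the comparison to which the power and the 0.05 belong. A single follow-up in Figure 1 would settle the visit. It would not settle whether scores or changes are compared, or supply a baseline adjustment. A schedule with several visits would not by itself make one of them primary.

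**Conclusion.** The point holds as a specification defect in the primary comparison. The text leaves its time point and score form open, and the stated test is unadjusted for a baseline value that the trial already has.

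The effect on the error rate is conditional. It is none with one follow-up, about 8-9% with two and 11-12.5% with three, for correlations of 0.5-0.7. At a correlation of 0.9 it falls to 6.8% and 8.1%. The number of visits, the correlation, equal allocation and two-sided testing are all assumptions. It is not shown that the trial will test repeatedly or that N = 70 is wrong. The plan should be changed because the remedy is cheap and removes the choice of visit after the fact.

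**What to change.** 1. In Outcome measures, name one scheduled RMDQ assessment as primary, before outcome data are compared by group. The end of the eight-week treatment period is one candidate, if the RMDQ is measured then. If the main claim is longer term, name that visit instead. Label all other visits secondary.
2. In the sample-size sentence, tie the three-point difference and the 80% power to that visit and that analysis.
3. In Statistical analysis, make the single confirmatory test a comparison at that visit adjusted for baseline RMDQ, two-sided at 0.05. Use ANCOVA if there is one follow-up, or the corresponding contrast of a mixed model if there are several. Report the adjusted difference in RMDQ points with its 95% confidence interval.
4. Keep Mann-Whitney on the change score at the same visit as a sensitivity analysis.

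The cost is a few sentences. No extra participants, visits or staff are needed, and the baseline RMDQ is already collected. The downside is that a significant result found only at another visit becomes a secondary result.

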## Discussion

The aim of this study is to compare SMCE and general exercises within the sub-group of patients with MD in the sub-acute stage of LBP. The main study question is which of the two exercise programs is more effective in reducing the disability associated with LBP.

European clinical guideline for management of chronic LBP recommends that more research is required to develop tools to improve the classification and identification of specific clinical sub-groups of chronic LBP patients [5]. Good quality RCTs are then needed to determine the effectiveness of specific interventions aimed at these specific risk/target groups. There is a need to evaluate sub-acute non-specific LBP and need to study interventions aimed at subgroup of patients with MD.

This RCT aims to test the hypothesis whether patients within a sub-group of MD benefit more through a specific individually tailored exercise program than through general exercise.

The participants in this trial are unique population; a sub-classification of MD or movement control impairment in non-specific LBP patients will show that the findings of this trial can confidently be applied to similar populations. The comparison is between two exercise programs and therefore the data should not be used to make inferences about the effectiveness, compared to no intervention, of any of the treatments. The findings can assist care providers, therapists and people with sub-acute LBP to make rational decisions about treatment. Care providers will need to take into account how the interventions are administered.

The study protocol of investigating patients with sub-acute LBP is important. If there are effective ways of preventing LBP to become chronic, the high costs of treating patients could be avoided.

This study has several limitations. The treating physiotherapist or subjects cannot be blinded, however because there is no accepted standard therapy, it is not truly known which therapy is better. The amount of the home exercises is totally dependent the motivation of the subject to perform the given exercise program which could influence the outcome of this study. Core stability represents a spectrum of exercises [64]. The comparison group includes a group of core stability exercises, core stiffness exercises, that involves an element of control of the spine. This means that both groups have an intervention that is cognitively attempting to control the position of the spine, although they also have fundamental differences in their application and potential benefits. This study includes subjects with recurrent, sub-acute LBP. Some of these individuals may spontaneously recover [4]. With a small sample size, the results would have to be interpreted with caution. There are several aspects of the study which influence the external validity. The application of the interventions within the study relies on the skills of the treating physiotherapist. Physiotherapists could learn to teach general exercise program, but the assessment and rehabilitation of MD is not taught in all undergraduate courses and post graduate training is required. This study will use five treatment sessions, however it may take longer for some patients to learn the SMCE well enough to change the movement patterns and decrease disability. In practice, greater than five sessions is likely possible, however if the SMCE are not effective in reducing disability, it is not known what would happen with a longer rehabilitation time frame with more sessions. In clinical practice, time and costs often limit the time that a physiotherapist can spend with a patient. It may not be appropriate to physiotherapists to spend forty-five minutes with patients as was done in this study. This could influence the application of learning the SMCE.

The main study question is which of the two exercise programs is more effective in reducing the disability associated with LBP.
